## Abstract

**Background:**

Many patients do not fully regain motor function after ischemic stroke. Transcranial direct current stimulation (TDCS) targeting the motor cortex may improve motor outcome as an add-on intervention to physical rehabilitation. However, beneficial effects on motor function vary largely among patients within and across TDCS trials. In addition to a large heterogeneity of study designs, this variability may be caused by the fact that TDCS was given as a one-size-fits-all protocol without accounting for anatomical differences between subjects. The efficacy and consistency of TDCS might be improved by a patient-tailored design that ensures precise targeting of a physiologically relevant area with an appropriate current strength.

**Methods:**

In a randomized, double-blinded, sham-controlled trial, patients with subacute ischemic stroke and residual upper-extremity paresis will receive two times 20 min of focal TDCS of ipsilesional primary motor hand area (M1-HAND) during supervised rehabilitation training three times weekly for 4 weeks. Anticipated 60 patients will be randomly assigned to active or sham TDCS of ipsilesional M1-HAND, using a central anode and four equidistant cathodes. The placement of the electrode grid on the scalp and current strength at each cathode will be personalized based on individual electrical field models to induce an electrical current of 0.2 V/m in the cortical target region resulting in current strengths between 1 and 4 mA. Primary endpoint will be the difference in change of Fugl-Meyer Assessment of Upper Extremity (FMA-UE) score between active TDCS and sham at the end of the intervention. Exploratory endpoints will include UE-FMA at 12 weeks. Effects of TDCS on motor network connectivity and interhemispheric inhibition will be assessed with functional MRI and transcranial magnetic stimulation.

**Discussion:**

The study will show the feasibility and test the efficacy of personalized, multi-electrode anodal TDCS of M1-HAND in patients with subacute stroke patients with upper-extremity paresis. Concurrent multimodal brain mapping will shed light into the mechanisms of action of therapeutic personalized TDCS of M1-HAND. Together, the results from this trial may inform future personalized TDCS studies in patients with focal neurological deficits after stroke.

**Supplementary Information:**

The online version contains supplementary material available at 10.1186/s13063-023-07234-y.

## Introduction

### Background and rationale

Ischemic stroke (IS) remains a global challenge and two-thirds of stroke patients show continued motor deficits which impact activities of daily living and quality of life [1]. Early-initiated rehabilitation training is central to recovery of motor function after IS [2, 3]. Transcranial brain stimulation (TBS) as an add-on to neurorehabilitation in the early subacute phase after IS (within the first 4 weeks after stroke onset) might result in faster and better recovery by optimizing the underlying neuroplastic processes, which may be more susceptible during the subacute phase post-stroke [4]. However, the use of a TBS technique to improve rehabilitation has to be feasible for patients and implementable in a clinical setting.

Transcranial direct current stimulation (TDCS) has been tested as a non-invasive tool to improve neurorehabilitation. The electric currents that TDCS can induce in the cortex through scalp electrodes result in a minor shift in the membrane potential and thereby a modification of the intrinsic neuronal network activity [5–7]. The pyramidal neurons in the area located under the anodal electrode are suggested to increase in excitability through depolarization of both the soma and the afferent axons while the pyramidal neurons located under the cathodal electrode decrease in excitability through hyperpolarization of the soma and afferent axons [8, 9]. These modulations in the membrane potential are thought to modulate behavior [10] and enhance neural plasticity by stimulating synaptic connections and long-term potentiation processes [11, 12].

Previous clinical trials have demonstrated that TDCS of the primary motor cortex (M1) may improve upper-extremity function in both subacute and chronic stroke patients, when applied concurrent with rehabilitation training. Ipsilesional anodal TDCS with the traditional montage of two square electrodes have been most widely examined [13–15], but contra-lesional cathodal TDCS [16, 17] and dual-TDCS [18] also has been studied. Across these studies, TDCS was applied to target the hand region of the primary motor cortex (M1-HAND) of either the healthy or the affected hemisphere, and current intensity is usually fixed between 1 and 2 mA across all subjects. However, according to meta-literature, up to 50% of patients are non-responders to the intervention [19], and only limited evidence of a significantly increased effect of TDCS compared to sham regarding upper-extremity rehabilitation [20–22]. Such lack of effects may associate to the *one-size-fits-all approach* which might miss the area thought to be targeted by TDCS (e.g., M1) both regarding location and current strength necessary to induce shifts in the membrane potential of the neurons in the target area. In addition, TDCS is often combined with either robot-assisted rehabilitation [22] or virtual reality [23] which may further confound the interpretation of the results.

Using individual magnetic resonance imaging (MRI) scans, electric field modeling enables a precise estimation of the electric field distribution in the brain during transcranial electrical brain stimulation and an optimization of electrode placement and dosing of interventional TDCS [24–27].

Patients with post-stroke upper extremity disability show an impaired motor network structure including a reduced excitatory influence from pre-motor brain areas and disinhibition of the contra-lesional M1-HAND [28, 29]. The interhemispheric imbalance between precentral motor cortices tends to improve with motor recovery and is often completely restored in patients with full recovery [28–30]. It is however unclear whether this imbalance facilitates or hinders motor recovery [29, 31].

### Objectives

The main hypothesis of this study is that patient-tailored anodal TDCS targeting the ipsilesional M1-HAND during supervised upper extremity training will result in greater improvements in upper-extremity function, measured by difference in change in FMA-UE score, compared to sham stimulation. It is furthermore hypothesized that patient-tailored TDCS is feasible to use for stroke rehabilitation in a stroke unit at a hospital setting.

Additionally, it is hypothesized that motor improvements correlate with the degree of normalization of functional motor connectivity and interhemispheric inhibitory interaction as revealed by task-related functional MRI and TMS. We will also assess the degree of corticospinal tract (CST) integrity measured by transcranial magnetic stimulation (TMS) and diffusion-weighted MRI (DWI) to explore how structural impairment in the corticospinal tract relates to the efficacy of anodal TDCS.

### Trial design

The study will be a parallel double-blinded two-arm randomized sham-controlled trial. In addition to usual care (preventive medication, advice on self-managed lifestyle changes, and municipal rehabilitation) the intervention group will receive two times 20 min of patient-tailored TDCS concurrent with supervised upper-extremity training for three times per week for 4 weeks in a 1:1 allocation ratio. The framework applied is exploratory.

## Methods: participants, interventions, and outcomes

### Study setting

Patients will be recruited during their admission at the Stroke Units of three participating University Hospitals of the Capital Region of Denmark (Region Hovedstaden): Copenhagen University Hospital Herlev and Gentofte, Copenhagen University Hospital Rigshospitalet, Copenhagen University Hospital Bispebjerg and Frederiksberg. Recruitment started in August 2022.

Patients will undergo routine clinical examinations for stroke patients and stroke subtype will be classified according to the Trial or Org 10,172 in Acute Stroke Treatment (TOAST) classification [32]. Patients will be grouped according to a cortical- or subcortically located stroke lesion for follow-up analyses that will explore the effect of stroke location on the potential beneficial effects of real TDCS.

See Table 1 for routine clinical examinations and demographic information collected.

**Table 1 Tab1:** Routine examinations and demographic information

Routine examinations	Demographics
Blood samples Chest x-ray Magnetic resonance imaging of the brain Carotid ultrasound Computerized tomography (CT) angiography or MRI time of flight (TOF) of the brain to screen for intracranial stenosis Electrocardiogram (ECG) Holter monitoring for 72 h Transthoracical ecocardiography (TTE) in patients < 65 years	Medical history Prior and concurrent medication Smoking status (former, active never smoker) Alcohol consumption (weekly), Pre-morbid modified Rankin Score Education level, Pre-morbid walking status, Pre-morbid living arrangements Marital status, Stroke severity Active hand movement at stroke onset Ability to walk unassisted at stroke onset Administration of thrombolysis (IVT) or reperfusion therapy (EVT) prior to inclusion

### Eligibility criteria

Inclusion criteria for the patients are ischemic stroke lesion either located cortically or subcortically in the large hemispheres, symptoms presenting with any degree of arm paresis, age ≥ 18 years, able to speak and read Danish, and able to give informed consent and index stroke within 28 days of inclusion.

Exclusion criteria are > 50% stenosis of extra- or intracranial vessels, > 1 cerebral infarct or stroke event during admission, cerebral aneurysms or cerebral arterio-venous malformations, stroke location outside the large hemispheres, cognitive dysfunction interfering with the ability to participate, history of seizures, epilepsy or epilepsy in first-degree family, anxiety, dementia, alcohol- and drug abuse, headaches > 16 days per month or migraine as these can be provoked by TDCS and TMS, current use of neuro-receptor/transmitter modulating medication, medication reducing seizure threshold or prior adverse effect to TDCS or TMS, contraindications to MRI, or claustrophobia.

### Intervention — rehabilitation training

A training program designed to meet the individual needs and challenges of the patient will be planned in a pretraining session. Based on the evidence-based practice within neurorehabilitation the training will be goal-directed, repetitive, and task-specific [33, 34] with a focus on reaching, grip, and fine motor skills. See Supplemental Materials S1 for a detailed description of the exercise framework.

The participant will be encouraged to remain physically active. Furthermore, the patients will be instructed in two to four individual home-based exercises which they will do between intervention days. The number of repetitions and time spent on home-based exercises will be recorded in a pen-and-paper log by the patient in order to record compliance (see Supplemental Material S1).

There are no concomitant care or interventions (including medications) prohibited during the trial for both arms.

Intervention sessions will take place at Copenhagen University Hospital Herlev supervised by a trained occupational- or physiotherapist. Each training session will consist of two sessions of 20 min exercise with concurrent TDCS separated by a small break (≈5 min). The type of TDCS, active or sham TDCS, will be determined by randomization after inclusion of the patient.

The exercises will advance in difficulty gradually as the patient improves which is consistent with earlier findings that progressive practice improves motor skill learning and increased corticospinal plasticity [35, 36].

### Intervention — transcranial direct current stimulation

Focal anodal TDCs of the ipsilesional M1-HAND will be given via a multiple-electrode 4 + 1 montage using 20 mm round rubber electrodes (Richardson et al. [37], Alam et al. [38]) and a DC-STIMULATOR PLUS connected to a neuroConn Equalizer Box (NeuroConn, Ilmenau, Germany). Electrodes will be fixed on the scalp using Ten20® conductive paste in an approximately 0.2 cm thick even layer and covered by a net cap. The scalp will be prepped prior to electrode placement with NuPrep® skin scrub and alcohol swaps. The target electrode will be positioned over the ipsilesional hand knob area and the four cathodal return electrodes will be positioned equidistant surrounding like a ring with 60 mm to the target electrode (see Fig. 1).

**Fig. 1 Fig1:**
[figure not shown]
NeuroConn DC-STIMULATOR PLUS and an example of TDCS 1 + 4 round electrode montage

Active stimulation mode consists of 30 s ramp followed by 19 min of stimulation and 30 s ramp-down to 0 mA. On the sham mode, there will be 30 s ramp-up and 30 s ramp-down [10, 39] to a small 50-μA sinusoidal current followed by 30 s ramp-down to 0 mA. See Fig. 2. The 50-μA current does not induce any physiological effects but allows impedance testing whereby the display at the DC stimulator appears identical in active and sham mode. The sham mode was preprogrammed in the DC-STIMULATOR at neuroConn Technology.

**Fig. 2 Fig2:**
[figure not shown]
Diagram displaying the active and sham mode of transcranial electrical stimulation

TDCS intensity will be calculated based on personalized electrical field models and adjusted to reach a field intensity of 0.2 V/m in the target area [40]. Both, the center electrode position, and current intensity will be individualized to each patient. We anticipate that personalized electrical field modeling will result in current intensities of 1.5–2.5 mA in most participants. TDCS intensity will not exceed a maximum current of 4.0 mA.

### Criteria for discontinuation

Patients not able to complete > 75% of the intervention sessions, patients with side effects from TDCS (such as severe headache following each intervention session), patients not able to complete the MRI scans, readmission with recurrent stroke or admission with another condition that contradicts TDCS, or upper-extremity exercise will be discontinued from the study.

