### Participant timeline

All patients will be assessed at baseline directly after enrolment and at follow-up1 (after the 4 weeks of intervention has ended) and follow-up2 (12 weeks post-interventions).

See Table 3 for SPIRIT-figures of study procedures, Fig. 4 for a study flowchart, and Fig. 5 for a graphical synopsis of the study protocol.

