### Statistical methods

All variables will be tested for normal distribution prior to analysis and logarithmically transformed if necessary. If data diverge from the normal distribution after transformation non-parametric testing will be performed. All tests will be two-sided and P < 0.05 will be considered significant. Data will be analyzed using Microsoft Excel 2010 (Microsoft Corporation, Redmond, WA, USA), *R* (version 3.6.1)*,* and REDCap or similar software. Statistical planning is conducted in a corporation with a biostatistician.

All data will be analyzed for the intention-to-treat population. All patients with complete outcome data will be analyzed according to the group they were randomized to. All available data for each patient will be included in the analysis. Missing data will be analyzed using imputation. Estimated treatment effects will be calculated based on a constrained longitudinal data analysis (cLDA) which will provide a result unbiased by values missing at random.

At follow-up 1 and follow-up 2 immediately after and 12 weeks after the intervention, respectively, a linear mixed model analysis will be used for both primary and secondary outcomes using cLDA. No other independent variables will be included in the analysis. The effect size will be calculated as mean change from baseline to follow-up and given as mean estimates of differences with a 95% confidence interval (CI). Patients that do not show up for a follow-up visit will be counted as missing values for the specific assessment point meant to be evaluated at that particular follow-up visit.

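### The discontinuation criteria remove randomised patients from the study, not only from stimulation, which conflicts with the declared intention-to-treat analysis and leaves a bias of unknown direction

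*Protocol article*

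**What the plan says.** The Criteria for discontinuation section of the protocol article names the triggers in one sentence. It begins "Patients not able to complete > 75% of the intervention sessions, patients with side effects from TDCS" and illustrates the side-effect rule by severe headache after every session. It then adds "patients not able to complete the MRI scans", recurrent stroke leading to readmission, and admission for another condition that rules out stimulation or arm training. The consequence is the same for all of them: the patients "will be discontinued from the study".

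Statistical methods states "All data will be analyzed for the intention-to-treat population". The next sentence narrows this: "All patients with complete outcome data will be analyzed according to the group they were randomized to". The section then says that all available data are used, that missing data are imputed by a method it does not name, and that treatment effects come from a cLDA, described as unbiased when values are missing at random. No further independent variables enter the model.

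Primary outcome sets the endpoint as change in FMA-UE from baseline to the end of the 4-week intervention. Participant timeline gives three assessments: baseline, follow-up 1 after the intervention, and follow-up 2 twelve weeks later.

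**The concern.** Stopping treatment and leaving the study are treated as one event. Apart from any failure at a baseline scan, the triggers arise after treatment has been assigned, and several may be related to treatment or to recovery. An intention-to-treat comparison needs the outcome of exactly these patients, but the rule as written ends their participation. A missed MRI scan can also end it, although FMA-UE is a bedside assessment that needs no scan.

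If the rule is followed, the primary result describes patients who tolerated and attended the programme, under an intention-to-treat label. A week-4 score that was never taken cannot be recovered at the analysis stage.

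**Working it through.** **1. The session rule.** Trial design gives "supervised upper-extremity training for three times per week for 4 weeks in a 1:1 allocation ratio", so 3 × 4 = 12 sessions. More than 75% means more than 0.75 × 12 = 9, that is at least 10. A patient who completes 9 or fewer meets the criterion, so the third missed session is enough.

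**2. The plan's own figures.** Sample size gives a difference of 5 points, SD 3–4, α = 0.05, and 80%, which is labelled a Type II error and read here as power. With SD 4, two-sided, n per arm = 2 × (1.960 + 0.842)² × 4² / 5² = 10.05, rounded up to 11. The t-test version gives 11.09, rounded up to 12, which matches the stated 12. The 15 per arm corresponds to 12 / (1 − 0.20), an implied loss of 20% in each arm. The concern does not alter these figures.

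**3. What the model can recover.** A patient removed before week 4 has a baseline score and nothing later. Under missing at random, the cLDA in effect gives that patient the week-4 mean of completers in the same arm with the same baseline. Tolerance, attendance and recurrent stroke are not in the model. Imputation from the same information adds nothing. Even an imputation that used attendance or side effects would have little to learn from, because the rule itself removes the patients in whom those events occur.

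**4. Size of the bias.** Let d be the share removed before week 4 in an arm, and D the amount by which removed patients improve less than completers, beyond what baseline predicts. The completers' mean then exceeds the mean of all randomised patients by d × D. With the same D in both arms:

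bias = (d_active − d_sham) × D, positive values favouring active.

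The documents give neither d by arm nor D, so all rows below are assumptions.

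| Lost, active | Lost, sham | D (points) | Bias (points) |
|---|---|---|---|
| 20% | 20% | any | 0 |
| 20% | 10% | 3 / 5 / 8 | +0.3 / +0.5 / +0.8 |
| 20% | 0% | 3 / 5 / 8 | +0.6 / +1.0 / +1.6 |
| 20% | 5% | 2 / 4 | +0.3 / +0.6 |
| 30% | 5% | 4 | +1.0 |
| 10% | 20% | 4 | −0.4 |

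The ends are not limits. With D = 8, the last row would give (0.10 − 0.20) × 8 = −0.8.

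**5. Type I error.** Completers' t-tests were simulated with no true difference, SD 4 and 20,000 runs, as a stand-in for the cLDA.

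| Lost, active / sham | D | 15 randomised per arm | 30 randomised per arm |
|---|---|---|---|
| 20% / 20% | 4 | 4.9% | 5.1% |
| 20% / 5% | 2 | 5.7% | 5.8% |
| 20% / 5% | 4 | 6.8% | 8.3% |
| 30% / 5% | 4 | 8.8% | 13.5% |

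**6. Equal loss is not enough.** Suppose completers gain 5 points from active TDCS and discontinued active patients gain nothing. The effect over all randomised patients is 5 × (1 − d): 4.5, 4.0 or 3.5 points at 10%, 20% or 30% discontinued. An estimate resting on completers would still report 5. The bias vanishes only if loss is equal and also related to outcome in the same way in both arms.

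**The case against.** The strongest reply is that the analysis is not a plain completers' comparison: available data are kept, imputation is planned, and the cLDA uses baseline scores from everyone. This stands as a description, but the planned methods give only limited protection, because a patient removed before week 4 has no post-baseline value.

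The session and MRI rules apply alike to both blinded arms. The side-effect rule is illustrated by severe recurring headache, not by any sensation. Patients with frequent headache, migraine, claustrophobia or MRI contraindications are excluded beforehand, and skin analgesia is used. All of this may limit unequal loss, and it stands.

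The article condenses a full protocol that might provide for continued assessment. But the point does not rest on a missing detail. The article states that patients leave the study, and this conflicts with its stated population.

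Three stronger readings are tempting and not supported:

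- **The comparison is biased toward active TDCS.** No section gives removals by arm or outcomes after removal. The 20% allowance applies to each arm, and equal loss with the same D gives zero.
- **Baseline scan failures are losses after randomisation.** The stimulation type "will be determined by randomization after inclusion of the patient", and "All patients will be assessed at baseline directly after enrolment". Neither sentence says whether randomisation comes before the baseline MRI, and the schedule and flow figures that could settle it are not shown.
- **Every MRI failure costs the primary endpoint.** The last scan comes 12 weeks after the intervention, so failure there need not remove a week-4 score.

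**Conclusion.** The conflict between Criteria for discontinuation and Statistical methods is firm and rests on the text alone. If the rule is followed, the primary estimate depends on completers and on a missing-at-random assumption that is doubtful for removals due to side effects, poor attendance or recurrent stroke. Neither cLDA nor imputation cures this.

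The size and direction of the bias are unknown. The scenarios worked here run from about −0.4 to +1.6 points against the expected 5, and they depend wholly on assumed loss rates and outcome gaps. A bias toward active is plausible if the current causes more removals there: active mode delivers 19 minutes of stimulation, while sham delivers ramps and a 50-μA current that the article describes as without physiological effect. That remains a possibility and is not shown by the documents.

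**What to change.** Leave the clinical reasons for stopping as they are, and change what follows from them:

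- In Criteria for discontinuation, state that meeting a criterion ends stimulation and/or training only and that the patient stays in the study.
- Measure FMA-UE at follow-up 1 and follow-up 2 in every randomised patient who has not withdrawn consent, whatever number of sessions or MRI scans was completed.
- In Statistical methods, analyse all these patients as randomised and remove the restriction to complete outcome data. The cLDA and imputation then cover only values that truly could not be obtained.
- Use the > 75% rule only to define a per-protocol sensitivity set.

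The cost is an amendment during recruitment and a few extra assessments at visits already in the schedule. The sample-size calculation is unchanged. The estimated effect may be slightly diluted because some analysed patients will have had little stimulation, as in step 6 of the working. That diluted figure is the one an intention-to-treat analysis is meant to estimate. Scores already missed under the current rule cannot be recovered, so the amendment is worth more the earlier it is made.
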